## Abstract

**Introduction:** Treatment of autoimmune pancreatitis (AIP) is based solely on consensus and has yet to become standardized. Consequently, therapeutic regimens vary greatly between countries and centers, and largely depend on the experience of the physician. At this moment, the optimal regimen for inducing disease remission and preventing relapse is unknown.

**Objectives:** The primary objective of this study is to describe current treatment regimens used in Europe, and to compare their effectiveness in inducing remission and preventing and treating relapse. The secondary objectives are: to identify risk factors for relapse; to assess the diagnostic accuracy of the Unified-AIP criteria; to assess the performance of the M-ANNHEIM score for predicting relapse; and to assess long-term outcomes including pancreatic exocrine insufficiency and pancreatic cancer.

**Methods:** This is an international, retrospective, observational cohort study, performed in over 40 centers from 16 European countries. Eligible are all patients diagnosed with AIP from 2005 onwards, regardless of the used diagnostic criteria. Data on study subjects will be retrieved from the hospital's electronic medical records and registered with a standardized, web-based, electronic case report form (eCRF). To compare the effectiveness of treatment regimens in inducing remission, preventing relapse, and treating relapse, subjects will be stratified in groups based on: type of therapy; initial therapy dose; cumulative therapy dose; therapy tapering speed and duration; and having received maintenance therapy or not.

**Ethics and Dissemination:** Ethical and/or institutional review board approvals are obtained by all participating centers according to local regulations. The study complies with the General Data Protection Regulation (GDPR). All manuscripts resulting from the study will be submitted to peer-reviewed journals.

**Conclusion:** This is the first pan-European retrospective registry for AIP. It will produce the first large-scale data on treatment of European patients with AIP, providing answers on the use and effectiveness of treatment regimens. In the future, this collaboration may provide a network for continuation into a prospective European registry.

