All AIP subtypes respond dramatically to steroid treatment (up to 99% in the different cohorts) (11–14), but the optimal dose to induce remission remains controversial. Reported induction doses have ranges between 30 and 60 mg daily (11–14) Recently, other therapeutic options, that induce B-cell depletion, have also been employed in inducing AIP remission, with promising results (15, 16). In a cohort from France, the reported efficacy was 94% with two infusions given in most patients (17). However, in spite of the dramatic response to initial treatment, the risk of relapse within 1 year from disease remission ranges between 30 and 50% (12), being higher in type 1 than in type 2 AIP patients (12). Several risk factors for AIP relapse have been proposed, but have not been validated prospectively (11, 12, 18, 19). Due to the high frequency of relapse after induction, some authors recommend maintenance treatment with low-dose steroids or immunomodulators, but the patient group that would benefit from maintenance is currently unknown (20–26).

Thus far, data on the epidemiology and natural history of AIP are still scant due to its rarity and its relatively recent appraisal. Most of the data comes from Asian or North-American cohorts, while data on large European cohorts are lacking. As a consequence, treatment options applied in Europe are largely based on retrospective studies from Asian and North-American patients.

We established the PrescrAIP (A Pan-European Study on Current Treatment Regimens of Auto-immune Pancreatitis) study network to retrospectively describe the current status of AIP treatment in Europe on a large scale. In addition, our effort will create the opportunity for a subsequent international prospective registry that will be able to provide definite answers in the future. In particular, in this retrospective multicentre study, we aim to define and compare the AIP treatment regimens used throughout different European centers, highlighting their differential impact on disease remission and long-term outcomes. These results will foster our knowledge of this rare disease, yielding to better patient care.

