## Objectives

The primary objective of this study is to describe AIP treatment regimens across Europe, and to compare the effectiveness of treatment regimens in inducing remission, preventing and treating relapse. The secondary objectives include identifying risk factors for relapse, assessing the diagnostic accuracy of the U-AIP criteria (6), assessing the performance of the M-ANNHEIM score for predicting relapse (19), and assessing long-term outcomes including pancreatic exocrine insufficiency and pancreatic cancer. Thirdly, we are aiming to assess whether standard treatment was altered due to pre-existing diabetes mellitus, determine the prevalence of diabetes mellitus before and after steroid treatment, assess glycemic control in patients with diabetes mellitus and to describe the clinical, radiological and pathological characteristics of a cohort of patients diagnosed with AIP through pancreatic resection.

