## Methods

### Study Design

This is an international, retrospective, observational cohort study including all AIP patients. We used the Pancreas2000 framework (www.pancreas2000.org) to create a study network starting with the six centers in the PrescrAIP core group. Additional European centers with expertise in the treatment of AIP patients have been recruited, accumulating to a total of 44 collaborating centers.

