### Study Endpoints

Our primary endpoints consist of remission of disease (defined as the absence of clinical symptoms and the resolution of pancreatic abnormalities on imaging), relapse of disease, relapse rates compared between patients with a low or a high dose regimen, cumulative maintenance therapy dose and relapse-free survival time. Our secondary study endpoints are gold standard diagnostic tools of AIP compared to U-AIP, the prevalence of pancreatic exocrine insufficiency and the cumulative incidence of pancreatic ductal adenocarcinoma. The diagnosis of diabetes mellitus [as defined by the American Diabetes Association (27)] either before or after steroid treatment is our tertiary study endpoint.

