### Statistical Analysis

Continuous, non-normally distributed values will be presented as median and interquartile range (IQR), unless otherwise specified. Discrete variables will be presented as frequency (percentage). Normal distribution of continuous variables will be assessed with the Kolmogorov–Smirnov algorithm. Normally distributed variables among the different groups will be compared using the Student's *t*-test. Non-normally distributed variables will be compared using the Mann–Whitney *U*-test. Categorical variables will be analyzed by the Fisher's exact test or chi-square test.

To compare remission rates, relapse rates, relapse-free survival and long-term outcomes between participants, we will stratify participants according to the date of diagnosis, meeting the different diagnostic criteria, the type of treatment, the glucocorticoids starting dose, the cumulative dose, tapering speed, and treatment with maintenance treatment.

Moreover, to assess the impact of the treatment effect being part of the diagnostic criteria, we will perform sensitivity analyses comparing the study outcomes between those classified as AIP regardless of the steroid trial, and those in whom the diagnosis was dependent on the steroid trial. Sensitivity analyses will also be performed to compare the study outcomes including or excluding individuals that do not meet any available diagnostic criteria, and those classified as NOS-AIP.

Kaplan-Meier curves will be used to assess time-to-relapse. Time-to-relapse will be compared between subgroups using the log-rank test. Univariable and multivariable analyses with a backward selection procedure will be performed to identify possible predictors for relapse, based on a Cox-proportional hazards regression model. A significance threshold of *P* < 0.05 will be used.

Data from national pancreatic cancer registries will be used to determine age- and sex-specific incidence rates for pancreatic ductal adenocarcinoma. Standardized incidence ratios (SIRs) will be then calculated by obtaining the ratio of the observed to the expected number of cases, and 95% confidence intervals (95% CIs).

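### The primary comparisons of non-randomised regimens are given only unadjusted tests; the one multivariable model is a backward-selected search for relapse predictors, so confounding can stay in the main answer

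*Protocol article*

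**What the plan says.** The Objectives section of the protocol article sets a comparative primary aim: "to compare the effectiveness of treatment regimens in inducing remission, preventing and treating relapse". Study Endpoints makes one such contrast a primary endpoint: "relapse rates compared between patients with a low or a high dose regimen". The design is not randomised: "This is an international, retrospective, observational cohort study including all AIP patients". On how treatment was chosen, the Abstract says that "therapeutic regimens vary greatly between countries and centers, and largely depend on the experience of the physician".

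The Statistical Analysis section names the t-test and Mann-Whitney test for continuous variables. For binary outcomes it says "Categorical variables will be analyzed by the Fisher's exact test or chi-square test". Time to relapse is compared between subgroups by log-rank test. Participants are grouped by five treatment variables (type, starting dose, cumulative dose, tapering, maintenance) and by two others (when the diagnosis was made and which criteria were met). The only multivariable analysis is a Cox model: "Univariable and multivariable analyses with a backward selection procedure will be performed to identify possible predictors for relapse". Identifying risk factors for relapse is listed under the secondary objectives.

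Two further statements bear on confounding. The Introduction describes relapse risk as "being higher in type 1 than in type 2 AIP patients", and it reports that some authors advise maintenance because relapse after induction is frequent. A further objective is to "assess whether standard treatment was altered due to pre-existing diabetes mellitus".

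**The concern.** When physicians choose the regimen, groups defined by regimen can differ in prognosis before treatment starts. A chi-square or log-rank test compares the groups as they stand, so any difference in case mix is read as a difference between regimens. Grouping patients by treatment variables defines the exposure; it does not control for anything.

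The article supplies the ingredients of confounding itself: a prognostic factor (AIP type), an indication tied to the outcome (maintenance and relapse risk), and treatment choice that follows country and centre. Neither AIP type nor centre or country is among the grouping variables. The planned sensitivity analyses and the stated limitations deal with diagnostic misclassification and the steroid trial. Confounding by indication is not mentioned.

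The Cox model does not close the gap. It covers relapse only, it serves a different objective, and data-driven selection may drop a confounder or the treatment term itself. At stake is the study's headline answer on which regimens work better.

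**Working it through.** The article gives no sample size, event count or power figure, so there is nothing of its own to reproduce. The check is a comparison of objective and method, followed by illustrations of size.

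**Objective against method**

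| Primary comparison | Method named | Adjusted model named |
|---|---|---|
| Inducing remission | Fisher or chi-square | None |
| Preventing relapse | Fisher or chi-square, log-rank | Only the backward-selected predictor search |
| Treating relapse | Fisher or chi-square | None |

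**Illustration 1: size of the crude bias.** All inputs are assumed: share of type 1 = 0.70; P(high dose | type 1) = b = 0.60 to 0.70; P(high dose | type 2) = 0.40; relapse r1 = 45-50% in type 1 and r2 = 15-30% in type 2; no dose effect. Overall relapse is then between 0.7×0.45 + 0.3×0.15 = 36% and 0.7×0.50 + 0.3×0.30 = 44%, inside the 30-50% one-year range in the Introduction.

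- Type 1 share among high-dose patients: 0.7b / (0.7b + 0.3×0.4).
- Type 1 share among low-dose patients: 0.7(1−b) / (0.7(1−b) + 0.3×0.6).
- Crude relapse in a group: r2 + (r1 − r2) × type 1 share.

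Low end (b = 0.60, r1 = 45%, r2 = 30%): shares 0.42/0.54 = 0.778 and 0.28/0.46 = 0.609. Relapse 41.7% versus 39.1%; ratio 1.065; difference 2.5 points.

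High end (b = 0.70, r1 = 50%, r2 = 15%): shares 0.49/0.61 = 0.803 and 0.21/0.39 = 0.538. Relapse 43.1% versus 33.8%; ratio 1.274; difference 9.3 points.

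**Illustration 2: false-positive rate of an unadjusted two-proportion test, no true effect.** The ends of the 30-50% range are used, by assumption, as low- and high-risk strata of equal size. N is also assumed.

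| Treated, high-risk / low-risk | Crude relapse, treated vs untreated | N = 200 | N = 400 | N = 800 |
|---|---|---|---|---|
| 60% / 40% | 42% vs 38% | 0.08 | 0.13 | 0.21 |
| 70% / 30% | 44% vs 36% | 0.21 | 0.37 | 0.64 |
| 80% / 20% | 46% vs 34% | 0.41 | 0.69 | 0.94 |

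A larger registry does not shrink the bias; it makes the wrong result more likely to be significant.

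**Illustration 3: crude, fixed and backward-selected Cox models.** Simulation with 300 replicates, true treatment HR 1, and four assumed binary confounders, each with HR 1.4 for relapse and odds ratio 2.0 for treatment. Elimination at P<0.05 is assumed.

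| | N = 200 | N = 400 | N = 800 |
|---|---|---|---|
| Crude HR | 1.20 | 1.25 | 1.24 |
| Type I error, crude | 0.13 | 0.29 | 0.46 |
| Type I error, fixed covariates | 0.05 | 0.06 | 0.04 |
| Type I error, backward selection | 0.08 | 0.10 | 0.07 |
| At least one confounder dropped | 99% | 90% | 53% |

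The Monte Carlo standard error is about √(0.05×0.95/300) = 0.013 near 5%. The excess of backward selection over the fixed model is therefore modest and imprecise, while the excess of the crude model is clear at N = 400 and 800.

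**Dropping a confounder is not the same as large bias.** Under an assumed 0.05 threshold, the chance of dropping a factor with HR 1.3 and prevalence p is 1 − Φ(ln 1.3 × √(events × p(1−p)) − 1.96). For p = 0.2 to 0.4 this gives 75% to 65% with 150 relapses and 56% to 40% with 300. Omitting one such factor, with treatment in 60% of those who have it and 40% of those who do not, moves the crude ratio only to 1.082/1.043 = 1.04 (p = 0.2) or 1.150/1.092 = 1.05 (p = 0.4).

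**The case against.** The strongest reply is that this is a condensed article. Covariate lists and weighting methods usually sit in a full protocol or analysis plan, and neither is shown. That would answer a complaint about missing detail. It does not answer this one, because the section does state which tests are used and how the multivariable model is built, and for the primary contrasts the stated methods are unadjusted.

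Several stronger readings are tempting, and the text does not support them:

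- A reader might infer that covariates are eliminated at P<0.05. That figure is a general significance threshold in a separate sentence; no elimination rule is given. The drop probabilities above hold only if it is assumed.
- A reader might infer that the grouping variables are used one at a time. The article does not say whether they are crossed. Crossing time of diagnosis and diagnostic criteria with treatment would give limited control, but would not cover AIP type, severity, organ involvement or centre.
- A reader might infer that treatment is kept out of the Cox model. It may be a candidate, so some adjusted relapse estimate may appear. Remission and treatment of relapse would still have none.
- A reader might infer that sicker or type 1 patients are known to receive other starting doses. No passage says so, and altered treatment in diabetes is posed as a question. The documented drivers are country, centre and physician, plus relapse risk, in general terms, for maintenance.

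The Discussion also calls the study descriptive and leaves definite answers to prospective work. That tempers the claims, but it does not remove a comparative primary objective or the Abstract's promise of answers on effectiveness.

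**Conclusion.** The concern holds in this form: the plan states a comparative primary objective in a non-randomised cohort, assigns it unadjusted tests, and names no adjusted model for remission or for treatment of relapse. Its one multivariable model is a backward-selected predictor search for a secondary objective and cannot be relied on to keep confounders or the treatment term.

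The size is illustrative, because the article gives no allocation figures. Under the assumed AIP-type mix, the crude relapse ratio is 1.07 to 1.27 (2.5 to 9.3 points) with no true dose effect. The unadjusted tests do most of the harm; backward selection adds a smaller excess error. That the primary answer is exposed to confounding follows from the text; the actual direction and amount of bias cannot be known from it.

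**What to change.** Make an adjusted estimate the main result for each primary treatment contrast: Cox regression for time to relapse, and logistic regression for remission, including remission after treated relapse. Propensity or overlap weighting on the same covariates is an acceptable alternative.

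Fix the covariates in advance, measure them before the treatment being compared starts, and keep them whatever their P value: AIP subtype, age, sex, serum IgG4, other-organ involvement, presentation and imaging pattern, pre-existing diabetes, calendar period, and centre or country as a stratum or random effect. Centre or country belongs in the set because it is the driver of regimen choice that the article itself names.

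The Introduction reports steroid response of up to 99%. If remission as defined in Study Endpoints is also very frequent, a logistic model with this many terms may be unstable. Use a penalised fit, a reduced covariate set or weighting where events are few.

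Report the unadjusted tests as descriptive, and confine backward selection to the secondary risk-factor objective.

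The cost is plan wording, analysis time and somewhat wider intervals. Demographic, clinical, laboratory and radiological variables are already to be recorded in the eCRF (Assessment Variables). One practical check: a coded centre or country variable must survive the removal of identifiers at data export described under Ethics and Disseminations.

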## Introduction

Autoimmune pancreatitis (AIP) has recently been recognized as an immune-mediated disease of the pancreas with distinct features (1). It is a rare disease with an annual incidence of ~3.1/100,000, which varies substantially between geographical regions (2). To date, two types of autoimmune pancreatitis have been described (1). Type 1 AIP is the pancreatic manifestation of IgG4-related disease (IgG4-RD). It shares clinical and histological hallmarks with IgG4-RD, namely increased serum Immunoglobulin G4 (IgG4) levels, dense storiform fibrosis, and IgG4-positive plasma cell infiltration of the affected organ (3). Type 2 AIP is known as idiopathic duct-centric pancreatitis and is characterized by neutrophil-mediated duct destruction, in the form of granulocytic epithelial lesions (GEL) (4). Both types can cause abdominal pain and jaundice and can ultimately lead to chronic pancreatitis (1). This in turn, might even increase the risk of developing pancreatic cancer (5). Yet, the incidence of these complications has not been clearly established.

In the last two decades, several efforts have been made to establish diagnostic criteria (1, 6–8), which are all based on the combination of clinical, serological, and pathological features. Nevertheless, AIP cases are still missed or even mistaken for pancreatic ductal adenocarcinoma (9, 10). As such, sequelae of chronic pancreatitis with endocrine and exocrine insufficiency can develop or the diagnosis of type 1 and type 2 AIP is made after unnecessary surgery (11). In addition, a discrete percentage of AIP cases does not fulfill diagnostic criteria for type 1 or type 2 AIP and thus are referred to as Not-Otherwise-Specified (NOS) AIP (1).

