### Study Population

Every patient with an AIP diagnosis (type 1, type 2 or NOS-AIP) will be included, regardless of diagnostic criteria used (U-AIP, HISORt, ICDC). Patients with AIP diagnosed prior to 2005 will be excluded due to lack of uniformity in diagnostic standards.

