### Assessment Variables

At the time of inclusion, all relevant variables will be recorded in the eCRF. These will include variables on demography and epidemiology, disease characteristics (radiological, laboratory and clinical), the set of diagnostic criteria employed, treatment (type, dose, duration), and short and long-term clinical outcomes. The complete variable list and definitions are reported in Appendix 1. AIP subtypes will be defined following the analysis of the above-mentioned variables. Given that patients with elevated serum IgG4 but without other organ involvement or biopsy sample can potentially be misdiagnosed, a subgroup with these characteristics will be created. Then a sensitivity analysis with and without excluding this subgroup will be performed to evaluate potential differences in the outcomes.

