This project has several strengths. Based on a multicentre cohort, this pan-European AIP study will provide a large dataset, dealt by field experts. Indeed, the vast majority of AIP reports derive from North-American or Asian cohorts, with most likely distinct genetic or environmental features that might not be shared by European AIP patients. Therefore, our study will plausibly provide a more homogenous AIP population thus far not included in recent trials. Due to the rarity of AIP, multicentric collaboration offers the unique possibility of obtaining more reliable results since larger patients' cohort can be analyzed. Moreover, the electronic datasheet will guarantee data quality and safety and will also stimulate data homogeneity across the various very heterogeneous countries and practices.

The study does not come without limitations, it being a descriptive retrospective study. There is a risk of the clinical and diagnostic guidelines being applied differently throughout the recruitment period. To mitigate this, we have collected clinical symptoms, laboratory and radiological findings rather than using the derivative AIP subtyping of the clinician. For example, as in most institutions pancreatic biopsies are not performed, seronegative type 1 AIP confined to the pancreas could be misdiagnosed as type 2. Conversely, atypical type 2 AIP with elevation of serum IgG4 might be classified as type 1 AIP. By subgrouping patients according to clinical, histopathological (where available) and radiological findings we aim to better judge the AIP subtype of the patient we aim to better judge the AIP subtype of the patient and increase transparency and uniformity of the AIP diagnoses made. As the response to a steroid trial might in some cases establish the diagnosis of AIP incorrectly, we will perform a subgroup analysis in patients in whom the AIP diagnosis was based on the successful steroid trial. Hereby, we will be able to estimate the effect of this group on the overall results of our analysis. In addition, we will be enabled to perform sensitivity analyses in that distinct subgroups, as described above. Lastly, many patients have a long follow-up, which should strengthen the true AIP diagnosis.

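### The pancreatic cancer SIR does not separate cancers found soon after AIP diagnosis, so cancers first labelled AIP could bias it upward if they are counted

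*Protocol article*

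**What the plan says.** The Protocol article, Study Endpoints, lists "the cumulative incidence of pancreatic ductal adenocarcinoma" among the secondary endpoints. The Objectives place pancreatic cancer among the long-term outcomes.

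Statistical Analysis defines the comparison with the general population: "Data from national pancreatic cancer registries will be used to determine age- and sex-specific incidence rates for pancreatic ductal adenocarcinoma", and then "Standardized incidence ratios (SIRs) will be then calculated by obtaining the ratio of the observed to the expected number of cases", with 95% confidence intervals. It attaches no lag and no rule for early cancers to the observed count.

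Study Population sets eligibility: "Every patient with an AIP diagnosis (type 1, type 2 or NOS-AIP) will be included, regardless of diagnostic criteria used". The only exclusion stated there is a diagnosis before 2005.

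The article recognises wrong AIP diagnoses in two places:

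- Assessment Variables says that patients with raised IgG4 but neither other organ involvement nor a biopsy may be misdiagnosed. For them, "a sensitivity analysis with and without excluding this subgroup will be performed to evaluate potential differences in the outcomes".
- The Discussion concedes the point for steroid trials: "As the response to a steroid trial might in some cases establish the diagnosis of AIP incorrectly". It also notes that most institutions do not take pancreatic biopsies.

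Statistical Analysis adds sensitivity analyses by dependence on the steroid trial, by failure to meet any criteria set, and by NOS-AIP.

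**The concern.** The question behind the SIR is whether AIP, through chronic pancreatitis, raises the later risk of pancreatic cancer. A cancer that was already there when the AIP label was given says nothing about that risk. Under the stated eligibility such a patient belongs to the cohort, and under the stated formula the cancer is an observed case unless a rule not given in the article removes it.

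The planned sensitivity analyses help only in part. A mislabelled cancer that met a criteria set without a steroid trial, and that falls outside the IgG4-only and NOS groups, stays in all of them. Time since AIP diagnosis is what best separates a cancer present from the start from one that developed later, and no planned analysis uses it for the SIR.

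Pancreatic cancer is rare enough that the expected count in a cohort of this kind is likely to be small. A few such cases could then determine how the result reads.

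**Working it through.** **Inputs.** The article states no SIR, expected count, cohort size, mean follow-up or background rate, so there is no figure of its own to reproduce. Every number below is an assumption made for illustration.

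**Step 1: expected cases.** E = N × mean follow-up × rate.

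- Low: 500 × 5 × 20/100,000 = 0.5.
- High: 1,500 × 5 × 60/100,000 = 4.5.
- Middle: 1,000 × 5 × 40/100,000 = 2.0.

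Each early mislabelled case adds 1/E to the SIR, so three add 3/4.5 = 0.67 to 3/0.5 = 6.0.

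**Step 2: effect on the interval at E = 2.** Exact Poisson limits are χ²(0.025; 2O)/(2E) and χ²(0.975; 2O+2)/(2E).

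| Observed | SIR | 95% CI |
|---|---|---|
| 2 true cases | 2/2 = 1.0 | 0.12 to 3.61 |
| 2 true + 4 mislabelled | 6/2 = 3.0 | 1.10 to 6.53 |

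**Step 3: general form.** If a fraction m of the cohort has cancer labelled AIP and it surfaces during follow-up, then

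SIR observed = SIR true + m / (mean follow-up × rate).

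Cohort size cancels out of the point estimate. Check against step 2: m = 4/1,000 = 0.004, and 0.004/(5 × 0.0004) = 2.0, which is the rise from 1.0 to 3.0.

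For 4 to 6 years of follow-up and 20 to 60 per 100,000 per year:

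| m | Added to the SIR |
|---|---|
| 0 | 0 |
| 0.1% | 0.28 to 1.25 |
| 0.5% | 1.39 to 6.25 |
| 1% | 2.78 to 12.5 |

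**Step 4: what a 12-month lag does.** Take 1,000 patients, 6 years, 40 per 100,000, a true SIR of 1 and m = 0.5% (5 cases).

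- Counted from AIP diagnosis: E = 1,000 × 6 × 0.0004 = 2.4; O = 2.4 + 5 = 7.4; SIR = 7.4/2.4 = 3.08. For scale, 7 observed against 2.4 gives 2.92 (1.17 to 6.01).
- First 12 months only: E = 0.4; O = 0.4 + 5 = 5.4; SIR = 5.4/0.4 = 13.5.
- After 12 months: E = 1,000 × 5 × 0.0004 = 2.0; O = 2.0; SIR = 1.0.

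The return to 1.0 assumes that all mislabelled cancers surface within 12 months and that all patients are followed for at least that long.

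**The case against.** A reader might infer that the plan counts cancers from the day of AIP diagnosis and that the SIR is therefore inflated. The document does not support this as a fact. No section fixes the start of person-time or of case counting, and a rule could sit in Appendix 1, a full protocol or an analysis plan, none of which is shown. Inflation also needs some mislabelled cancers to exist and to be counted; if there are none, it is zero. Sites may have dropped patients whose AIP label was later revised, which would lower the count. The bias therefore has to be stated conditionally.

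The Introduction's remark that "AIP cases are still missed or even mistaken for pancreatic ductal adenocarcinoma" shows that the two diseases are confused, but in the opposite direction. The admissions of false AIP diagnoses in Assessment Variables and the Discussion do not name cancer as the true disease. They support the possibility, not its frequency.

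A reader might also take the expected rates to ignore country. They come from national registries, which already implies country-specific rates. Calendar period, censoring rules and the type of confidence limits are details commonly left to an analysis plan and are no finding here.

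It is also fair to say that the article does address misdiagnosis, that the cancer endpoint is secondary in a study that calls itself descriptive, and that no decision rule is tied to the SIR. All of this limits the weight of the point. It does not remove it: the article sets out the SIR and a list of misdiagnosis analyses, and that list lacks the one based on time since diagnosis.

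**Conclusion.** The point holds in conditional form. As described, the SIR sets all observed cases against expected cases in a cohort open to any AIP diagnosis, and early cancers are not separated. If they are counted, cancers first labelled AIP bias the SIR upward as a measure of long-term risk, and the sensitivity analyses by diagnostic basis remove only part of that.

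The size cannot be derived from the document. Under the assumed ranges, even 0.1% mislabelled adds 0.28 to 1.25 to the SIR. At 2 expected cases, four mislabelled cancers are enough to move a true 1.0 to 3.0 with a lower limit above 1. These figures rest on assumed follow-up and background rates and on an unknown number of mislabelled cancers.

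**What to change.** State in Statistical Analysis when person-time and case counting start for the SIR. Report an SIR that excludes the first 12 months after AIP diagnosis from both observed cases and person-time, and show the 0-12 month SIR separately. The 12-month cut is a convention rather than a figure from the document, so it should be fixed before the cancer data are examined.

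The change is one of wording and analysis code. The lagged SIR needs the interval from AIP diagnosis to cancer or end of follow-up, which the expected count calls for in any case.

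The price is the first year of person-time. In the 6-year illustration, expected cases fall from 2.4 to 2.0, a loss of 0.4/2.4, or one sixth, and the interval widens somewhat. The lag does not recover patients whom sites left out after revising the diagnosis. Finding them would mean going back to records across 44 centres, and that is not part of this request.
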